# STUDY TREATMENT

Time from randomization to first treatment (surgery or first ART cycle) should be minimized with a goal of three months and should preferably not exceed six months. Complications due to treatments (IVF or surgery) will be register in the eCRF and treated according to clinical routine at each hospital.

EXPERIMENTAL TREATMENT

First line endometriosis surgery followed by ART such as IVF or ICSI.

STANDARD/CONTROL TREATMENT

First line ART such as IVF or ICSI.

SURGICAL PROCEDURE

Surgery will be performed at one of four nationally specialized centers in advanced endometriosis surgery (Södersjukhuset Stockholm, Sahlgrenska University Hospital Göteborg, Skånes University Hospital, Malmö/Lund, Uppsala University Hospital). Intraoperative AAGL endometriosis staging, #ENZIAN classification and Endometriosis Fertility Index (EFI) (31) will be recorded in the study protocol. Surgery will be conducted according to the ESHRE recommendations of surgery in endometriomas and deep endometriosis (32, 33). Surgery should be multidisciplinary when needed (colorectal surgeons and urologists). The goal of the procedure is to remove as many endometriotic lesions as possible while also minimizing negative impact on organ function, since endometriosis is a benign disease. Rectal endometriosis will be removed with rectal shaving, discoid or segmental resection depending on the size and placement of the lesion in the rectal wall. Laparoscopic cyst enucleation is considered the "golden standard" as it is associated with a low recurrence rate, significant pain relief, and increased chances of spontaneous conception (34). In cases where ovarian reserve is already diminished, more gentle methods such as ablation therapy with CO2 Laser/Plasma Jet or sclerotherapy could be employed (35-37). These methods can also be used in combination with conventional surgical cyst enucleation. The choice of surgical technique should be tailored to the individual patient's needs.

In Sweden in 2023, 9.9% of patients undergoing surgery for endometriosis within the framework of national highly specialized care experienced mild complications Clavien Dindo 1-2 (e.g. infection and hematoma at the surgical site), and 3.3% experienced serious complications Clavien Dindo 3 (e.g. bowel leakage, unexpected bladder injury, ureteral injury, or intra-abdominal bleeding requiring reoperation) (38). Serious complications may, in rare cases, necessitate further surgical interventions. The risk of complications varies slightly depending on the location of the endometriosis (38).

Patients undergoing surgery will need to delay ART treatment by two to three months in order to fully recover.

FERTILITY TREATMENT WITH ART

ART treatments will be carried out at Swedish reproductive units authorized to provide publicly funded fertility care. The majority of treatments are expected to take place at the university-affiliated reproductive clinics in Stockholm, Gothenburg, Skåne, and Uppsala. However, for participants residing in other regions of Sweden, undergoing treatment locally offers a significant advantage by reducing the logistical and emotional burden of long-distance travel to these central clinics. To ensure equitable access and minimize patient stress, regional ART centers will be considered when appropriate.

One IVF/ICSI-cycle is defined as the transfer of all the embryos created via that particular oocyte pick-up until pregnancy confirmation or until the failure of the last embryo transfer. In case of a cancelled cycle prior to oocyte pick-up it will not be counted. The duration of one IVF-cycle depends on the number of embryo transfers and typically ranges between two and nine months.

ART treatment: Women allocated in the ART arm will undergo up to three cycles of controlled ovarian stimulation (COS) followed by oocyte retrievals and embryo transfers. In Sweden, ART-treatment costs for women under the age of forty and without having children in current relationship are covered by the tax-funded healthcare system, with up to 3 IVF/ICSI treatments, given that they are considered medically meaningful, and that each stimulation is started before the woman turns 40 years of age (39). In case the treatment results in cryopreserved embryos, it is planned that they should be transferred prior to the start of any new COS. Women will be managed according to a routine clinical protocol at each reproductive unit. Stimulation protocols will be chosen individually by clinicians, taking into consideration age and ovarian reserve of each woman, as it is a standard routine in the collaborating Reproductive Units. No aspiration of endometrioma prior to oocyte pick-up will be performed. Antibiotic prophylaxis at the day of oocyte pick-up will be given according to local guidelines.

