- postpartum complications (defined as within 8 weeks postpartum): infections (endometritis, pelvic inflammatory disease, urinary tract infection, wound infection, sepsis), remaining conceptual tissue with and without surgical intervention, use of analgesics

COVARIATES

Potential covariates will be collected from patients’ medical records.

*Baseline characteristics:*

- Age (continuous and dichotomized as < and > 35 years)
- Infertility duration (months)
- Infertility due to social factors (yes/no)
- Infertility due to pain from endometriosis (yes/no)
- Infertility due to male factor (yes/no)
- Smoking (yes/no)
- Snuffing (yes/no)
- BMI (continuous)
- Hormonal endometriosis treatment (yes/no, if yes subtype of drug, duration of hormonal treatment prior to first surgery or ART)
- Parity (0, 1-2 or >2)
- previous caesarian sections (yes/no)
- previous abdominal surgery (yes/no)
- previous adnexal surgery (yes/no)
- previous uterine or cervical surgery (yes/no, type of surgery)
- smoking habits (yes/no)
- ovarian reserve (AMH<0.5ng/L, 0.5-3.5 ng/L and AMH >3.5ng/L)
- myoma (yes/no)
- time from randomization to first oocyte pick-up or surgery (depending on which treatment arm the patient is randomized to)
- ASA-class (1-2 or 3-4)
- Other diseases affecting the outcome: hypothyroidism, diabetes, bleeding disorders or thrombogenic diseases, hypertension, hyperprolactinemia

*Imaging specific data (Ultrasound MRI)*:

- #ENZIAN-score
- AAGL-score
- Adenomyosis (yes/no)
- antral follicle count (AFC)

*Perioperative data:*

- #ENZIAN score
- AAGL score
- EFI score
- Surgical procedure defined by KVÅ- codes: adnexal surgery (yes/no), surgery on deep endometriosis anterior compartment (yes/no) or deep endometriosis posterior compartment (yes/no)
- Colorectal surgery (yes/no, if yes rectal shaving, discoid resection or segmental resection)
- Urological surgery (yes/no, if yes bladder resection, reimplantation of ureter, end to end anastomose of ureter, shaving of ureter)
- Perioperative data: estimated blood loss, operative time, conversion rate
- Annual surgeon volume (number of advanced endometriosis surgeries per year)
- Cumulative surgeon volume (number of advance endometriosis surgeries in total at surgery)
- Consultant surgeon (yes/no, if yes which specialty)
- Reoperation (yes/no) until 2 months post-surgery
- Readmissions (yes/no) until 2 months post-surgery
- Hospital stays (days)
- Time to normal activity of daily life (ADL) (days)

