*Assisted reproductive technologies data (for each IVF/ICSI-cycle, max 3):*

- Complication – yes/no
- Type of complication (infection, ovarian hyperstimulation syndrome (OHSS), bleeding)
- Time from surgery to first oocyte pick-up
- Type of IVF protocols (GnRH agonist protocol/GnRH antagonist protocol)
- Total dose/mean daily dose of follicle stimulating hormone (rFSH) /human menopausal gonadotropin (hMG)
- Duration of IVF stimulation (days)
- Cancelled cycle (before or after oocyte pick up (OPU)) (excluding freeze all cycles)
- Reason of cancelled cycle
- Type of ovulation triggering [GnRH agonist (Gonapeptyl/Suprecur/Suprefact/Synarela) / Ovitrelle]
- Date of OPU
- Freeze all cycle (yes/no) and reason of that
- Number of retrieved oocytes (GV/MI/MII)
- Performed fertilisation method (ICSI/IVF)
- Sperm – fresh vs frozen
- Donor sperm – yes/no
- Origin of sperm – ejaculated/ epidydimal / testicular
- Oocytes – fresh vs frozen
- Number of inseminated oocytes
- Number of fertilised oocytes
- Number of good quality embryos defined according to Gardner criteria as AA, AB and BB for blastocysts (23) or top and good quality based on the number of blastomeres, the fragmentation rate and the multinucleation of blastomeres for cleavage stage embryos (24).
- Number of frozen blastocysts (D5 or D6)
- Date for fresh embryo transfer
- Embryo age at fresh embryo transfer (D2, D3, D4, D5 or D6)
- Number of embryos transferred (SET/DET)
- Type of embryo transfer (Fresh/Frozen)
- Type of protocols for Frozen-thawed ET (Natural Cycle (NC), HRT, Letrozol-stimulated, gonadotropinstimulated)
- Use of GnRH downregulation in Frozen-thawed HRT cycle (yes/no, number of days)
- Total estrogen dose and type of estrogen preparations in HRT FET-cycle
- Endometrial thickness prior to embryo transfer in HRT-FET
- Cycle day of endometrial thickness measurement in HRT-FET
- P progesterone level on the day of ET in HRT-FET
- Date of frozen ET
- Urinary pregnancy test (positive/negative)
- Gestational age at pregnancy ultrasound
- Fetal heartbeat at ultrasound (present/absent)
- Number of foetuses
- Number of gestational sacs
- Result foetus 1 (miscarriage, abortion, ectopic pregnancy, delivery)
- Date for delivery / end of pregnancy foetus 1
- Result foetus 2 (miscarriage, abortion, ectopic pregnancy, delivery)
- Date for delivery / end of pregnancy foetus 2
- Result foetus 3 (miscarriage, abortion, ectopic pregnancy, delivery)
- Date for delivery / end of pregnancy foetus 3

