# STUDY FLOW CHART

# SCHEDULE OF EVENTS TABLE

| Procedures | **Baseline** | **Enrolment** | **1 month prior to surgery or start of first ART cycle^1^** | **Surgery^2^** | **2 months postoperative visit^2^** | **1:st oocyte retrieval** | **2 months after 1:st oocyte retrieval** | **2:nd oocyte retrieval** | **2 months after 2:nd oocyte retrieval** | **3:rd oocyte retrieval** | **2 months after 3:rd oocyte retrieval** | **Visit, phone call or questionnaire 3 years after first treatment (surgery or first ART cykle)** |
| --- | --- | --- | --- | --- | --- | --- | --- | --- | --- | --- | --- | --- |
| **Informed consent oral and written** | x |  |  |  |  |  |  |  |  |  |  |  |
| **Demographics** |  |  | x |  |  |  |  |  |  |  |  |  |
| **Record ultrasound and/or MRI staging according to AAGL and #ENZIAN staging system** | x |  |  |  |  |  |  |  |  |  |  |  |
| **Randomization** |  | x |  |  |  |  |  |  |  |  |  |  |
| **Record surgical procedure according to AAGL and #ENZIAN staging system** |  |  |  | x |  |  |  |  |  |  |  |  |
| **Record intraoperative complications^3^** |  |  |  | x |  |  |  |  |  |  |  |  |
| **Hospital stay** |  |  |  | x |  |  |  |  |  |  |  |  |
| **Record 8 weeks postoperative complications^4^** |  |  |  |  | x |  |  |  |  |  |  |  |
| **EHP-30, EQ5D and NRS scale^5^** |  |  | x |  | x | x | x | x | x | x | x | x |
| **Primary outcome (CLBR)** |  |  |  |  |  |  |  |  |  |  |  | x |
| **Secondary outcome/IVF cycle^6^** |  |  |  |  |  |  | x | x | x | x | x | x |

^1^ start of FSH injections ^2^only first line surgery group ^3^According to Classic ^4^According to Clavien Dindo ^5^Endometriosis Health Profile and Numeric Rating Scale ^6^LBR, PR, number of oocytes retrieved, fertilization grade, number of blastocysts

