# STUDY ENROLLMENT

SCREENING PROCEDURE AND PARTICIPANT IDENTIFICATION

All women with stage III-IV AAGL endometriosis with infertility referred and/or eligible for surgery and/or ART-treatment such as IVF or ICSI will undergo screening for this trial. The results of this screening will be documented in a screening log. After obtaining oral and written informed consent, patients will be registered and randomized. Registration data will be entered to an electronic Case Report Form (eCRF).

STAGING

At baseline, a specialized transvaginal and abdominal ultrasound examination, supplemented with transabdominal ultrasound if indicated will be performed according to the International Deep Endometriosis Analysis (IDEA) group recommendations (25) to identify endometriosis lesions. Ultrasound and, if needed, magnetic resonance imaging (MRI) findings will be classified using the #ENZIAN and AAGL classification system (4, 6)**.**

The presence of adenomyosis will also be documented and characterized according to the Morphological Uterus Sonographic Assessment (MUSA) group recommendation (26, 27) . Women with and without suspected adenomyosis will receive the same treatment protocols. Presence of adenomyosis will not influence allocation but will be considered during the discussion of the final analysis of study results.

The use of hormonal treatment for endometriosis, prior to the surgery/ first ART-treatment or between the surgery and ART-treatment, will be documented and considered in the discussion of the outcomes.

INCLUSION CRITERIA

- Age 18 - 38 years old
- Endometriosis AAGL stage III-IV
- Referred or eligible for ART-treatment such as IVF or ICSI, independent of infertility diagnosis (28) (including sperm donation cycles for social reasons) and/or infertility due to dyspareunia/dysmenorrhea caused by endometriosis
- Body mass index 18-35 kg/m^2^
- Patients who have signed an approved Informed Consent

EXCLUSION CRITERIA

- Previous surgery for endometriosis except diagnostic laparoscopy.
- Previous IVF/ICSI-cycles (including prior fertility preservation cycles)
- Hemato- and/or hydrosalpinx
- Clear indication for surgery such as ureteral stenosis or intestinal sub-occlusive symptoms
- Suspicion of malignancy
- Submucosal fibroids (The International Federation of Gynecology and Obstetrics (FIGO) 0-1, any size) or intramural fibroids (FIGO 2-5, > 4 cm largest diameter of the largest myoma) (29)

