**Additional analysis**

– Exploratory subgroup analyses will not be adjusted for multiplicity.

– Safety outcomes will be summarized descriptively by treatment group (frequency, severity, relation to treatment).
– All available data will be used, including outliers.
– Missing outcome data will be handled under the missing-at-random assumption via maximum likelihood in mixed models; for regression models requiring complete covariates, complete-case analysis will be applied.

Covariates

Primary and secondary outcomes will be adjusted for prespecified covariates (age, BMI, AMH, ART type, center), chosen based on clinical relevance and prior evidence.

POWER CALCULATION AND SAMPLE SIZE

The sample size calculation was based on a two-sample comparison of proportions with a two-sided α=0.05 and 80% power. Based on observational data (18, 19), the cumulative live birth rate (CLBR) after three IVF cycles was assumed to be 55% in the ART-only group and 71% in the surgery+ART group (relative risk ≈1.29). This yields a required sample size of 142 participants per arm (284 total). Allowing for 20% attrition, the planned total sample size is 350 participants.

The necessary sample size for this study is estimated to 323 patients to accommodate a statistical analysis method. This estimation uses the 'pwr' package in R, specifically employing the power.prop.test method, which is designed to compare two proportions. This method is more aligned with contemporary statistical practices and provides a clear, transparent methodology for determining the required sample size based on expected success rates.

This means inclusion of 29 patients from/each center/year and 15 surgeries/year. In a Swedish study published in 2022 the prevalence of endometriosis in patients referred for ART-treatment was 21.8% and 17.2% of women had DE (14). In 2021 almost 10 500 IVF cycles were performed in Sweden, while more than 5 500 of those were first-time IVF/ICSI with autologous gametes ((46) Figure 22).

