# INTERIM ANALYSIS AND STOPPING RULES

An independent safety and monitoring board (DSMB) will conduct one interim analysis when 175 patients have been enrolled in the study and completed either their surgery or first IVF treatment, whichever occurs first. Because each participant has a three-year follow-up and recruitment will be completed within three years, only a limited proportion of primary outcomes will be available at the interim analysis. The analysis will therefore primarily address recruitment feasibility, participant safety including comparison of complication rates between study centers.  The DSMB will monitor adverse events in both arms. For surgery, expected complication rates have been described previously in this protocol (9.9% Clavien–Dindo grade 1–2, 3.3% grade ≥3), while ART carries a different spectrum of risks (e.g. ovarian hyperstimulation, infection, or bleeding). A substantially higher-than-expected complication rate in either arm, major discrepancies between centers or other safety concerns may prompt the DSMB to recommend protocol modifications or early termination.

Recommendations from the DSMB will exclusively be communicated to the Trial Steering Committee. Further details regarding the DSMB can be found in the DSMB charter (Appendix).

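### Complication recording is scoped to treatment harms while the safety analysis and DSMB remit are wider, so serious events from endometriosis left in place have no listed route into the three-year comparison

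*Protocol*

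**What the plan says.** The Study Treatment section of the protocol states: "Complications due to treatments (IVF or surgery) will be register in the eCRF". It is the only general statement of which complications are entered.

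The items listed under Study Objectives follow the same scope. Intraoperative complications are graded by CLASSIC, and postoperative ones by Clavien-Dindo to two months. The perioperative list adds "Reoperation (yes/no) until 2 months post-surgery" and "Readmissions (yes/no) until 2 months post-surgery". The ART list, kept per cycle, has a yes/no complication item followed by "Type of complication (infection, ovarian hyperstimulation syndrome (OHSS), bleeding". In the Schedule of Events the complication rows are marked only in the surgery and two-month postoperative columns, which are footnoted "only first line surgery group".

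Two other sections are wider. Additional analysis, under Statistical Considerations, says "Safety outcomes will be summarized descriptively by treatment group (frequency, severity, relation to treatment". Interim Analysis and Stopping Rules says "The DSMB will monitor adverse events in both arms". The DSMB charter adds that the board receives data on unexpected differences between arms and may recommend stopping for clear harm in either arm.

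The exclusion criteria show which disease events the protocol regards as serious: "Clear indication for surgery such as ureteral stenosis or intestinal sub-occlusive symptoms".

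**The concern.** The trial compares two strategies by intention to treat, and one of them leaves the lesions in place for some or all of the follow-up. A fair safety comparison therefore needs both the harm of operating and the harm of not operating. Recording that starts from treatment complications captures the first well and the second only in part.

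The passages also do not fit together. Relation to treatment is informative as a reported attribute only if unrelated events are collected, and a board cannot follow adverse events in both arms from a record confined to complications of IVF and surgery. This is a matter of data capture: no later analysis plan can report events that the case report form did not collect.

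At stake are the three-year safety table, which the protocol expects to inform guidelines, and to a lesser degree what the board sees at its interim review.

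**Working it through.** **Step 1. What each part of the protocol collects**

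| Section | What is recorded | Who and when |
|---|---|---|
| Study Treatment | Complications of IVF or surgery | Both arms, no window stated |
| Secondary outcomes | CLASSIC and Clavien-Dindo complications | Operated women, to two months |
| Perioperative data | Reoperation, readmission | To two months after surgery |
| ART data | Complication yes/no and type | Both arms, per cycle, up to three |
| Secondary outcomes | Infection after egg retrieval, graded by antibiotics, readmission or surgical intervention | Both arms |
| Schedule of Events, three-year contact | Questionnaires, live birth, cycle outcomes | Both arms; no adverse-event row |
| Long-Term Follow-Up | Repeat endometriosis surgery, from a register | Consenting women, 10 years after inclusion |

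**Step 2. Tracing two events**

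*Surgery arm, bowel leakage soon after the operation.* It is a treatment complication, graded by Clavien-Dindo, and captured again as reoperation or readmission. It enters the safety table.

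*ART-first arm, bowel obstruction by endometriosis between two cycles, leading to admission and an operation.* It is not a complication of IVF or of trial surgery. It falls outside the postoperative window and is not an infection after retrieval. The three-year contact has no item for it. The operation might appear as a protocol deviation, as a cost, or in the optional register follow-up, but none of these is the three-year safety comparison. No route is listed.

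The gap applies in both arms: a late disease event after surgery has no listed route either. The tilt arises only if such events are commoner where lesions remain.

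**Step 3. Scale**

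The protocol gives no rate for serious disease events, so there is no stated figure to reproduce. What it does give:

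- planned total 350, allocated 1:1, so 350 / 2 = 175 per arm;
- serious surgical complications s = 3.3%, so 175 × 0.033 = 5.8 women.

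Let q be the rate of serious disease events in the ART-first arm and r the share of that rate remaining after surgery. Leaving ART complications out as if equal in both arms, and assuming no woman has both kinds of event:

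- difference as recorded (surgery minus ART-first) = s = +3.3 points, whatever q is;
- difference counting all serious events = (s + r·q) − q = s − (1 − r)·q.

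Both q and r are assumptions:

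| q | all events, r = 0 | all events, r = 0.5 |
|---|---|---|
| 0% | +3.3 | +3.3 |
| 1% | +2.3 | +2.8 |
| 2% | +1.3 | +2.3 |
| 3% | +0.3 | +1.8 |
| 5% | −1.7 | +0.8 |

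The two harms balance when (1 − r)·q = 3.3 points, that is, when surgery prevents about 5.8 serious disease events per 175 women. That needs q = 3.3% if surgery prevents all of them, and q = 3.3 / 0.5 = 6.6% if it prevents half. The table shows how the answer depends on q and r; it does not estimate the bias.

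**The case against.** The strongest reply is that the Study Treatment sentence is a positive instruction, not a definition of safety reporting. It excludes nothing and does not ask sites to judge cause before recording. Several fields are set by time window rather than attribution: reoperation, readmission and infection after retrieval are plain yes/no items. The ART items stand in a list of potential covariates that includes a general complication item, and the actual case report form is not shown. All of this stands. A reader might infer that only events judged to be treatment-related are registered, but the text does not say so. The document is inconsistent rather than plainly restrictive, and a missing field can be claimed only in the sense that none is listed.

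A reader might also infer that surgery is charged its harms with no credit for harms it prevents. That does not hold either. The background links advanced disease to pelvic infection after retrieval, a lower rate after surgery is a secondary objective, and these infections are graded up to surgical intervention in both arms. Obstetric complications, pain and quality of life are compared by arm too. None of these, however, captures organ obstruction or unplanned admission or surgery for the disease.

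The illustration is open to the objection that equal ART complications sit badly with the protocol's own hypothesis of fewer infections after surgery. If that hypothesis is right, the recorded difference may itself be below 3.3 points. Finally, safety is summarised descriptively and the formal test at the 5% level is on live birth, so no decision boundary depends on this comparison. That limits the consequence but does not close the gap.

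**Conclusion.** The point holds as an inconsistency with a practical consequence. Recording is scoped to treatment complications, while the safety analysis and the board's remit presuppose more. Followed as written, serious events from endometriosis left in place have no listed route into the three-year safety comparison. If such events are commoner without surgery, the comparison tilts against first-line surgery.

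The size cannot be computed from the documents. The +3.3 points and the break-even near six events per arm rest on the stated national surgical rate applying to this population, every woman in the surgery arm being operated on, and equal ART complications; the rest of the table also needs assumed disease-event rates. A reader might take the −1.7 entry as showing that the safety balance would reverse. It does not: of the values shown, the sign changes only at 5% with surgery preventing every event.

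The effect falls mainly on the final report. The interim review comes once 175 women have completed surgery or their first IVF treatment. By then early surgical complications will have occurred, but little of the three-year disease follow-up will have accrued. The primary endpoint is untouched.

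**What to change.** Reconcile the Study Treatment sentence with the Additional Analysis and Interim Analysis sections:

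- Record serious events in both arms (death, unplanned admission, unplanned operation, organ obstruction or loss) from randomisation to the end of the three-year follow-up, whatever the cause. Starting at randomisation also covers the wait for first treatment.
- Hold relation to treatment as a separate field, completed after the event is entered.
- Add a matching row to the Schedule of Events, including the three-year contact, for both arms.
- In the board's report and the final report, show any serious event by randomised arm first, with treatment-related events as a subset.

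The cost is a change of wording, a few case report form fields and modest extra entry by sites. Trial data are already drawn from medical records, with participants contacted where information is missing. The change affects recording only, not clinical care.
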